### Data management

All CRFs in triplicate will be reviewed by the investigators and CRA. The completed CRFs will be securely stored in a locked location and finally sent to two independent data administrators, who will responsible for data entry, inspection and management in a specified statistics center. Once the trial is completed, the Principal Investigator, Sponsor, data administrators and statisticians will perform a blind review to confirm the dataset. The final database will be locked and analyzed in line with the statistical analysis plan.

### Statistical analysis

The independent statistician will conduct the data analysis using SAS 9.4 software (SAS, Cary, NC, USA), in accordance with the statistical analysis plan for this trial. The primary analysis set for efficacy is the full analysis set (FAS) with an intention-to-treat (ITT) principle, in which all patients treated with at least one dose of study drug and who have a clinical observation record should be involved. According to an ITT principle, the last-observation-carried-forward (LOCF) imputation method will be used for missing data. Patients who fulfil the protocol without any major deviations will be included in the per-protocol set (PPS). And all participants who receive at least one dose of the study drug and for whom safety data are available will be included the safety set (SS). Baseline characteristics of all subjects will be analyzed using descriptive statistics for continuous variables and categorical variables. Primary efficacy will be analyzed by comparing outcomes among three groups. Outcomes among three groups will be compared using analysis of variance (ANOVA) and the Bonferroni method. Covariates designated as potential confounders will include age, gender, body mass index (BMI) and duration of symptomatic illness prior to enrollment. Time to fever relief, time to fever clearance and duration of all symptoms will be estimated by the Kaplan-Meier technique and compared by the stratified log-rank test. The improvement of TUM symptoms will be estimated by descriptive analysis for number and proportion of patients achieving clinical recovery. Prespecified subgroup analysis and sensitivity analysis involving covariance analysis will be used to evaluate the primary outcomes according to age and gender. In the multicenter trial, the Cochran-Mantel-Haenszel (CMH) test will be performed to analyze stratified variables. A two-sided *P* value <0.05 is considered as statistically significant.

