### Outcome measures

#### Primary outcomes

The primary outcome of the study is the time to fever relief, which is defined as the time (number of hours) from the first dose of the test drug until the axillary temperature drops by at least 0.5 °C. All patients are required to record their axillary temperature in the subject diary every 1 h within the first 6 h. Then, if the temperature is ≥ 37.3 °C, it should be recorded every 2–4 h, and if the temperature is < 37.3 °C, it should be recorded at 8 a.m. and 4 p.m. every day. If the temperature is < 37.2 °C and does not rise for 24 h, it does not need to be recorded. The investigator will check and collect the subject diary in which the data will be acquired and evaluated on the fourth day.

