### Sample size calculation

Using “One-Way Analysis of Variance F-Tests using Effect Size” in PASS (version 15.0.5), we estimate the sample size with a significance level of 0.05. To our knowledge, no previous study has reported the effective size related to the time to fever relief in our target population (patients with common cold). Thus, we used η2 as an alternative measure of effect size, calculated by:

σm^2^ / (σm^2^ + σ^2^)

to estimate the sample size [21–23]. Generally, the effect size can be defined as follows: η^2^ = 0.0099 ≈ 0.01 is a small effect; η^2^ = 0.0588 ≈ 0.06 is a medium effect and η^2^ = 0.1379 ≈ 0.14 is a large effect [21–23]. In the study, we would like to determine the sample size required to detect a medium effect when the power is 0.90. Therefore, a total sample of 204 subjects (68 in each group) would be required. Assuming an overall 15% drop-out rate, 80 subjects should be recruited in each group. Finally, the total sample size is determined to be 240 patients.

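### Time to fever relief, the single primary outcome, is given two tests (ANOVA with Bonferroni, and a stratified log-rank test) with neither named as decisive, and power is stated only for ANOVA

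*Protocol article*

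**What the plan says.** The protocol article has one primary outcome. Its Primary outcomes section defines time to fever relief as "the time (number of hours) from the first dose of the test drug until the axillary temperature drops by at least 0.5 °C". Temperatures come from a patient diary that is collected on the fourth day.

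The Statistical analysis section then gives two instructions that both reach this outcome.

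- First: "Primary efficacy will be analyzed by comparing outcomes among three groups", followed directly by "Outcomes among three groups will be compared using analysis of variance (ANOVA) and the Bonferroni method".
- Two sentences after that: "Time to fever relief, time to fever clearance and duration of all symptoms will be estimated by the Kaplan-Meier technique". The sentence goes on to say that the three outcomes are compared by a stratified log-rank test ("duration of all symptoms will be estimated by the Kaplan-Meier technique and compared by the stratified log-rank test").

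One two-sided 0.05 threshold covers everything. The only missing-data rule is LOCF.

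The Sample size calculation section uses a one-way ANOVA F-test in PASS at a significance level of 0.05: "we would like to determine the sample size required to detect a medium effect when the power is 0.90". Medium is taken as η² ≈ 0.06. That gives 204 patients (68 per group), raised to 240 for 15% drop-out. No hazard ratio, median or event count appears.

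**The concern.** With two tests on one primary outcome and no order between them, the result can depend on a choice made after the data are seen. That creates a second chance of success at an unadjusted 0.05. It also leaves the conclusion open whenever the tests differ, in a trial that may help to select the phase III dose.

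The tests also suit the outcome unequally. ANOVA needs a completed time for every patient. The protocol itself expects incomplete times: it assumes 15% drop-out, stops collecting at day 4, and makes provision for patients whose temperature has not fallen significantly by 48 h. For such patients, ANOVA must either leave them out or enter the censoring time as if relief had occurred then. LOCF does not help, because carrying a temperature forward produces no event time. Kaplan-Meier and the log-rank test handle these patients as censored. Yet the stated 0.90 power belongs to ANOVA.

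**Working it through.** **1. Reproduce the plan's figure.** Inputs from the Sample size calculation: three groups, α = 0.05, η² = 0.06, power 0.90, drop-out 15%. The noncentrality of the one-way F-test is λ = N·η²/(1 − η²).

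- N = 204: λ = 204 × 0.06/0.94 = 13.02, which gives power 0.904. With 67 per group the power is 0.8996, so 68 is the smallest size that reaches 0.90.
- Drop-out: 204/(1 − 0.15) = 240.

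Both figures are right for ANOVA. The unrounded η² of 0.0588 would give 69 per group (207), a trivial difference.

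**2. What the same patients give the log-rank test.** The protocol states no hazard ratio (HR), so the result is expressed as the HR detectable with 90% power. For a three-group log-rank test (2 df, α = 0.05) the required noncentrality is 12.654. With D events in equal groups it equals D × Var(log HR across arms). Assume that all 204 evaluable patients have an event.

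| Assumed pattern (high dose v placebo = HR) | Variance | ln HR | Detectable HR |
|---|---|---|---|
| Low dose midway on the log scale | (ln HR)²/6 | √(6 × 12.654/204) = 0.610 | about 1.84 |
| Both doses equal | 2(ln HR)²/9 | √(4.5 × 12.654/204) = 0.528 | about 1.70 |

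Events needed for 90% power at other HRs (low dose midway / both doses equal): HR 1.5 needs 462 / 347; HR 1.75 needs 243 / 182; HR 2.0 needs 159 / 119.

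For one dose against placebo, with 68 + 68 = 136 events and Bonferroni α = 0.025, the detectable HR is exp[(2.241 + 1.282)/√(136 × 0.25)], about 1.83.

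**3. Cost of leaving both tests open.** These are simulations with exponential relief times, an hourly grid and a 72 h limit, and with censored times entered into ANOVA as observed. Relief times, drop-out by arm and drop-out timing are assumptions; the protocol gives only the overall 15%.

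| No true effect | Either test significant |
|---|---|
| 204 patients, no drop-out, centre-stratified log-rank, medians 6 / 24 / 36 h | 5.6% / 7.1% / 6.6% |
| 80 per arm, 15% drop-out in every arm | about 6–8% |
| 80 per arm, drop-out 5/15/25% by arm, spread over 72 h | about 7–9% across repeated runs |
| 80 per arm, drop-out 5/15/25% by arm, all in the first 24 h | about 12–14% |

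In the last row the excess comes from ANOVA; the log-rank test stays near 5%.

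**4. With a true effect.** With mean times of 16/12/9 h, power is 0.85–0.88 for ANOVA and 0.89–0.91 for log-rank across runs. With HRs 1.0/1.3/1.6, 204 patients and 0–17% censoring, the two tests reach different verdicts in about 8–12% of trials. At 17% censoring, power is 0.55 for ANOVA and 0.60 for log-rank, a gap close to simulation error.

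**The case against.** The ANOVA sentence could be general, with the later sentence that names each time outcome governing. That reading is possible but weak. The ANOVA sentence directly follows the one on primary efficacy, and the sample size, discussed in terms of time to fever relief, uses ANOVA.

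A separate statistical analysis plan is cited and not shown, and it may name the decisive test. That stands as a caution. It does not remove the conflict, because the protocol itself fixes two methods for one outcome, and a plan written to accord with it could choose either.

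The strongest objection concerns size, and most of it stands. Relief is only a 0.5 °C fall over three days in patients enrolled at 38–39 °C, so censoring may be slight; the protocol gives no figure. If nearly everyone has relief, ANOVA can be computed and loses little. The two tests are strongly correlated, so the error rate is well below the 1 − 0.95² = 9.75% of two independent tests. This is also a phase II, dose-exploring trial.

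A reader might infer that the ANOVA result would reflect drop-out instead of drug effect. The calculations do not support that: ANOVA keeps power of 0.85–0.88 where log-rank has 0.89–0.91. What can be said is that ANOVA can be distorted when censoring is substantial or differs by arm.

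**Conclusion.** The conflict is real and lies in the text: one primary outcome, two tests at the same threshold, no order between them, and power stated only for the test that does not accommodate censored times.

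Its numerical effect is modest if censoring is low and similar across arms: about 6–8% of null trials would show at least one significant test, against a nominal 5%. A reader might take 12–14% as the expected inflation. That needs drop-out that is both early and unequal across arms, and the protocol assumes neither. With a real effect, the more practical consequence is that the tests can disagree, in about 8–12% of trials under the assumed hazard ratios.

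A reader might also infer that the trial is too small. The documents do not show that. The figures 204 and 240 are correct for ANOVA, and log-rank power was at least as high in the simulations. What is missing is a statement of what the trial can detect with the log-rank test. The figures of 1.84 and 1.70 assume that all 204 evaluable patients have an event; fewer events would raise them.

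**What to change.** Before unblinding, in the protocol and the statistical analysis plan:

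- Name the centre-stratified log-rank test as the only primary test of time to fever relief. Centre is the randomisation stratum.
- Keep the Bonferroni step, applied to two named comparisons: high dose versus placebo and low dose versus placebo, each at 0.05/2 = 0.025. Report stratified Cox hazard ratios with 95% confidence intervals.
- Censor patients without relief at their last temperature reading, and state that LOCF is not applied to the event time.
- Make ANOVA supportive, or remove it for the time outcomes.
- Restate power for the log-rank test with 204 evaluable patients (240 randomised): 90% power in the three-group test for a high-dose hazard ratio of about 1.84 with low dose midway, or 1.70 with both doses equal, if all 204 have an event. Give the adjusted pairwise figure beside it.

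How readings after permitted paracetamol count is a separate question that this change does not settle. The cost is wording and a short power statement; no new patients or data are needed.

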### Randomization and blinding

According to a stratified block randomization method, 240 patients are stratified by study center and randomly assigned to the high-dose group, low-dose group or placebo control group in a 1:1:1 ratio. The random sequence and the randomization list of each center will be generated by the independent specialist, using the PRCO PLAN function of the analysis system of SAS software (SAS, Cary, NC, USA). The independent drug administrator will assign numbered packs of study drugs to eligible patients in order by randomization list. The randomization sequence will be concealed in a lightproof sealed envelope, which will be kept by the leader and the Sponsor.

Participants, investigators and statisticians will be blind to the treatment allocation throughout the study. Test drugs and placebo will be identical in appearance, color and taste. All drugs are concealed in uniform packages with number labels. An emergency letter including the random sequence and assignment has been prepared in each center. In any emergency medical situation, such as serious adverse event or deteriorative condition, the unblinding process will be started after contacting the Sponsor and the primary investigator. The investigator should record the details of urgent unblinding and make sure the corresponding patient is excluded.

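### The covariate list and the ANOVA leave out study centre, the only stratification factor, and baseline axillary temperature; this costs efficiency, not validity

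*Protocol article*

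**What the plan says.** All places are in the protocol article.

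- **Statistical analysis** names four covariates: "Covariates designated as potential confounders will include age, gender, body mass index (BMI) and duration of symptomatic illness prior to enrollment". It does not say which model uses them.
- The same section compares the three groups by ANOVA with the Bonferroni method, and no covariate or centre term is given there. It also compares time to fever relief, time to fever clearance and symptom duration by a stratified log-rank test, without naming the strata, and plans a CMH test in connection with the multicentre design. Covariance analysis is mentioned only with the subgroup and sensitivity analyses, by age and gender.
- **Randomization and blinding** gives one stratification factor: "240 patients are stratified by study center". Under **Recruitment**, five sites contribute equal numbers, so 240/5 = 48 patients per centre and 48/3 = 16 per arm per centre.
- **Primary outcomes** defines time to fever relief as the hours from first dose to an axillary drop of at least 0.5 °C. **Time to fever clearance** uses an absolute threshold, below 37.2 °C and sustained for 24 h.
- **Inclusion criteria** admit temperatures of 38 to 39 °C and symptoms of at most 24 h. **Safety assessment** lists temperature among the baseline vital signs.

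**The concern.** Two variables with a clear claim to the adjustment set are missing from it.

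**Centre.** Stratified randomisation balances the arms within centre. If centres differ in outcome, the difference between arm means no longer carries centre variation, but the ANOVA's error term still does. The standard error is then too large, the test is conservative, and the benefit of stratifying is lost.

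**Baseline temperature.** The fever endpoints are read off a temperature curve that starts at the entry value. For clearance the dependence is direct: a patient entering at 38 °C has to fall by more than 38 − 37.2 = 0.8 °C, and one entering at 39 °C by more than 39 − 37.2 = 1.8 °C. The article itself treats position within this range as meaningful, since its symptom table scores 38 to 38.5 °C as 6 and higher values as 9. Yet baseline temperature appears in no analysis model described, while prior symptom duration, which entry restricts to 24 h, is listed.

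At stake is precision in a dose-finding trial whose sample size is set for the overall three-group test. Adjustment is also best fixed before unblinding, so that covariates are not chosen with the results in view.

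**Working it through.** **Inputs from the article.** Alpha: "we estimate the sample size with a significance level of 0.05", and "A two-sided *P* value <0.05 is considered as statistically significant". Power: "determine the sample size required to detect a medium effect when the power is 0.90". Effect size: "η^2^ = 0.0588 ≈ 0.06 is a medium effect". The planning test is a one-way ANOVA F-test with three groups and no covariates. Result: "a total sample of 204 subjects (68 in each group) would be required", raised to 240 for 15% drop-out.

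**Input not in the article.** The share R² of within-group outcome variance explained by centre and baseline temperature. It is assumed, over a range of 0 to 0.30.

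**Step 1: reproduce the plan.** f² = η²/(1 − η²) = 0.06/0.94 = 0.0638. Noncentrality = N·f² = 204 × 0.0638 = 13.02, with 2 and 204 − 3 = 201 df and critical F = 3.041.

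- Power is 0.904 at 68 per group and 0.8996 at 67, so 68 per group (204) is reproduced.
- With the unrounded η² = 0.0588 the answer is 69 per group (207), a trivial difference.
- Drop-out: 68/0.85 = 80 per group and 204/0.85 = 240, as stated.

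The stated size claims no gain from covariates, so omitting them does not make it wrong.

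**Step 2: add centre and baseline temperature to the linear model.** Centre takes 4 df and temperature 1, so the error df are 201 − 5 = 196. The noncentrality becomes 13.02/(1 − R²).

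| Joint R² (assumed) | Noncentrality | Power at 68 per group | Total N for 90% |
|---|---|---|---|
| 0 | 13.02 | 0.904 | 204 |
| 0.02 | 13.29 | 0.910 | 198 |
| 0.05 | 13.71 | 0.919 | 192 |
| 0.10 | 14.47 | 0.932 | 183 |
| 0.20 | 16.28 | 0.957 | 162 |
| 0.30 | 18.60 | 0.977 | 144 |

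Using 1 or 4 extra df instead of 5 changes power by no more than 0.0001.

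**Step 3: balance on centre but leave it out of the ANOVA.** The error mean square keeps the centre variance while the between-arm comparison does not. This is equivalent to testing against 3.041/(1 − R²), with R² now for centre alone.

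| Centre R² (assumed) | Effective critical F | Type I error | Power, centre omitted | Power, centre included |
|---|---|---|---|---|
| 0.05 | 3.20 | 0.043 | 0.908 | 0.919 |
| 0.10 | 3.38 | 0.036 | 0.913 | 0.932 |
| 0.20 | 3.80 | 0.024 | 0.922 | 0.957 |

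Stratification alone already recovers part of the power. If centre carried all of the R², the further gain from modelling it would be 0.932 − 0.913 = 0.019 at R² 0.10 and 0.957 − 0.922 = 0.035 at R² 0.20.

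**Step 4: pairwise comparisons.** At Bonferroni alpha 0.05/3 = 0.0167 and 68 per group, power depends on how the three means are spaced, which the article does not fix.

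- If two arms have equal means, d = √(4.5 f²) = √(4.5 × 0.0638) = 0.536 and unadjusted power is 0.76. It rises to 0.785, 0.81 and 0.86 at R² 0.05, 0.10 and 0.20.
- If the low dose lies midway, d = √(6 f²) = √(6 × 0.0638) = 0.619 for high dose against placebo, and unadjusted power is already about 0.88.

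Pairwise figures are therefore illustrations and not properties of the plan.

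**The case against.** Five points on the other side deserve weight.

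1. **Centre may already be handled in the time-to-event analysis.** A reader might infer that the stratification factor is ignored throughout. The article does not support that. The primary outcome is also compared by a stratified log-rank test, a CMH test is tied to the multicentre design, and centre is the only declared stratum. The natural reading is a log-rank test stratified by centre, and naming strata is often left to the analysis plan, which is not shown. This stands: the criticism of centre applies to the ANOVA and the covariate list, and for the log-rank test only confirmation is needed.
2. **Temperature may predict little.** A reader might infer that it is the strongest predictor of the primary outcome. Nothing in the article shows this. Entry spans only 1 °C, the outcome is measured in hours, and the event is a relative drop, so the association could be weak. It is more direct for clearance, a secondary outcome. This stands: baseline temperature is a directly relevant variable, and no more is claimed.
3. **The size rests on an assumed R².** This stands. Near R² = 0 there is no material gain.
4. **The arithmetic is for a linear model.** Scaling by 1 − R² does not transfer directly to a log-rank or Cox analysis, and no gain was computed for those. This stands.
5. **The list may not be exhaustive, and covariate choice is partly judgement.** The wording does leave room for additions. But the article chose to name four variables, and the two omitted here have a claim from the design itself.

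**Conclusion.** The point holds as one of efficiency. The named covariates and the ANOVA contain neither the only stratification factor nor the entry temperature from which the fever endpoints start.

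The size is conditional. Under assumed R² values of 0.05 to 0.20, overall linear-model power at 68 per group would be 0.919 to 0.957 instead of 0.904, and an ANOVA that ignores a prognostic centre would run at a type I error of 0.043 down to 0.024. If the two variables explain almost nothing, almost nothing is lost.

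It would be wrong to conclude that the comparison is biased, that the false-positive rate is inflated or that the sample size is in error. Randomisation protects validity, the effect on the ANOVA is conservative, and 204 and 240 both reproduce. It is worth correcting because both variables are already recorded and the cost is low.

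**What to change.** Before unblinding:

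- Confirm that centre is the stratum of the log-rank test.
- Include centre and baseline axillary temperature in the prespecified effect model for time to fever relief and time to fever clearance: a Cox model stratified by centre with temperature as covariate or, if ANOVA/ANCOVA is kept, centre and temperature terms in it.
- State which model uses the listed covariates, and keep age, gender, BMI and symptom duration for sensitivity analyses.

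Cost: a wording change with no new data. In the linear model it uses about 5 degrees of freedom, with virtually no effect on power even at R² = 0. A Cox model adds a proportional-hazards assumption. If the change is made in the protocol and not only in the analysis plan, it needs the approvals set out under Quality control (sponsor, site investigators and statisticians, then presentation to the ethics committee).

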## Discussion

To date, this study is the first randomized, double-blind, placebo-controlled trial to evaluate the efficacy and safety of Uighur medicine in treating the common cold. In Central Asia, TUM is one of the most common traditional medicines, which has benefited many people in China and the other countries. So far, most of TUM researches have focused on therapy of skin disease, urogenital disease, rheumatism, digestive system and respiratory system disease [24]. To our knowledge, there have been few reports of standardized clinical trials designed for use in TUM.

Binafuxi formula has been used in Xinjiang Uygur Autonomous Region of China for over 20 years and based on local clinical experience it has been proven effective in treating CCHS. Derived from five different regions in China, the results of our study will provide stronger evidence for wider use of Binafuxi granules. We designed this study to practice the methodology of syndrome differentiation for clinical research in TUM. According to the grading standard for TCM, we will first perform the TUM symptom graded score system in this trial, and then verify if it is feasible. This will provide a scientific quantitative standard to estimate the efficacy of TUM in treating the CCHS. In the light of TUM theory on the CCHS and the characteristics of Binafuxi, the time to fever relief and the duration of fever will be primarily observed in this study [17]. The efficacy both of Western medicine and TUM will be evaluated, so as to provide more powerful evidence for TUM therapy for the common cold.

Nevertheless, there are two potential limitations in this study. During the screening period, we will not confirm viral titers to exclude potential patients with influenza since this would largely delay patient enrollment for the study and potentially miss the best time to intervene. However, all the experienced physicians involved for this study will carefully evaluate patients to avoid mistakenly recruiting unsuitable participants. In accordance with the exclusion criteria, we will strictly exclude any participants with body temperature > 39°C and severe respiratory symptoms. Patients with chills and/or other influenza-like symptoms will be excluded or advised to be tested for the influenza virus. Furthermore, in this study, we will not explore the mechanisms underlying the CCHS and potential pathways through which Binafuxi may work in treating the common cold, which may need further research.

In conclusion, this protocol is rigorously designed for exploring the efficacy and safety of Binafuxi granules in treating the common cold with heat syndrome. As far as we know, this study will be the first multicenter, double-blind, placebo-controlled and randomized clinical trial of a Uighur medicine in treating the common cold. In addition, it will provide robust evidence for assessment of the efficacy and safety of Binafuxi granules in treating the CCHS, and may help in selecting the optimal therapeutic dose for the next phase III clinical trial.

